## Confidentiality

Data for this study will be entered into a secure database with data checks used during data entry to ensure data quality. Access to the study's data will be restricted to members of the study team by username and password. Research data will be collected from the participant and entered into the database only after written informed consent is obtained.

## Provisions to Monitor the Data to Ensure the Safety of Participants

The principal investigator and study team will assume responsibility for monitoring enrollment, adverse events, data completeness, outcome data, protocol non-compliance, and new and relevant information.

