### Intervention Components

OffTC intervention will implement the standardized 24-form simplified Taichi exercise regimen, developed by the National Sports Administration in 1956 based on Yang-style Taichi principles. Modifications will be implemented for balance-intensive movements to enhance safety while maintaining form integrity.

VRTC intervention will utilize identical 24-form simplified Taichi movements implemented through an immersive technological interface. The VR system will incorporate precise arm-length calibration to accurately track upper and lower extremity movement trajectories.

Application: Guided Tai Chi (Developer: Cubicle Ninjas, Version 1.2.74, Release date: May 21, 2019)

Platform: Meta Quest VR Headsets.

[Video Supplementary files]

[figure not shown]

[figure not shown]
CT will utilize a comprehensive platform targeting multiple cognitive domains: memory, attention, executive function, logical reasoning, and reaction time. The system will be implemented via a customized WeChat mini-program interface.

[figure not shown]

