## Procedures Involved

This study employs a prospective sequential, multiple assignment, randomized trial design. The 24-week SMART design comprises two 12-week phases. In the first phase, eligible participants will be randomly assigned to receive either offline Taichi plus cognitive training (OffTC+CT) or virtual reality Taichi plus cognitive training (VRTC+CT). Each intervention will consist of 1-hour weekly exercise combined with 1 hour weekly cognitive training.

At week 12, participants will be assessed for intervention mastery, with non-responders (defined as those subjectively unable to master the intervention content, scoring less than 3 on a 5-point Likert scale) being re-randomized to alternative or intensified interventions for the second 12-week phase. Responders in Group OffTC+CT will continue their original intervention protocol, while non-responders will be randomly assigned to either VRTC+CT or doubled doses of their original intervention (2OffTC+2CT). Similarly, responders in Group VRTC+CT will maintain their initial protocol, while non-responders will be randomly assigned to either OffTC+CT or doubled doses of their original intervention (2VRTC+2CT). The control group will receive only health education and routine care throughout the 24-week period.

The anticipated duration for individual participation in the study is 24 weeks (6 months). The duration anticipated to enroll all study participants is approximately 9 months (April to December 2023).

[figure not shown]

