## Risks to Participants

The potential risks associated with this study are minimal. Taichi exercise may cause mild muscle soreness or fatigue, particularly in participants who are not accustomed to regular physical activity. Virtual reality Taichi may cause mild dizziness or disorientation in some participants. These symptoms are typically temporary and resolve with rest.

The cognitive training component poses minimal risk but may cause mild frustration or fatigue in some participants. There is also a small risk of loss of confidentiality.

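### No common adverse-event enquiry is fixed across the arms, and the risk section omits falls although the intervention text takes a balance precaution whose reach into VR Taichi is unclear

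*Protocol*

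**What the plan says.** **Balance precaution.** Under Intervention Components, the offline Taichi paragraph states: "Modifications will be implemented for balance-intensive movements to enhance safety while maintaining form integrity". The next paragraph states: "VRTC intervention will utilize identical 24-form simplified Taichi movements implemented through an immersive technological interface". It then specifies the software ("Application: Guided Tai Chi", one named version) and says nothing further about the modifications.

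**Risks.** Risks to Participants opens with "The potential risks associated with this study are minimal". For Taichi it says: "Taichi exercise may cause mild muscle soreness or fatigue, particularly in participants who are not accustomed to regular physical activity". For VR it says: "Virtual reality Taichi may cause mild dizziness or disorientation in some participants". It adds frustration or fatigue from cognitive training, and loss of confidentiality. Falls and injury do not appear.

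**Monitoring.** Adverse events are mentioned once in the protocol, in the safety-monitoring section: "The principal investigator and study team will assume responsibility for monitoring enrollment, adverse events, data completeness, outcome data, protocol non-compliance".

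**Contact.** Under Procedures Involved, both active arms have one hour of Taichi and one hour of cognitive training a week. Some non-responders receive double from week 13. For control: "The control group will receive only health education and routine care throughout the 24-week period". Outcome Assessment sets cognitive assessments at baseline, week 12 and week 24.

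**Outcomes.** The primary outcome is the derived strategy, expressed as time allocated to each component. The secondary outcomes are average and individual treatment effects. None concerns safety.

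**The concern.** There are two linked problems.

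First, the protocol is not consistent with itself on balance. A precaution taken for safety in balance-demanding movements recognises a hazard, but the risk section lists nothing that could follow from loss of balance. VR Taichi is the modality for which dizziness and disorientation are named, and it is also the one for which the text does not say whether the precaution applies.

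Second, making someone responsible for adverse events does not ensure that they are found equally in every group. Staff who meet participants weekly will hear of events that nobody asks controls about. A difference in counts between active and control could then reflect opportunity to report as well as risk. The trial is meant to yield a recommended allocation of Taichi minutes, so readers will want to see harms beside benefit. Control-arm events that nobody asked about cannot be recovered by any later analysis.

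**Working it through.** The protocol states no harm rate and no safety figure, so there is nothing to reproduce. The check has four steps.

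**1. Balance and risk text side by side.** Intervention Components: balance-demanding movements are modified for safety (offline paragraph). Risks to Participants: soreness, fatigue, dizziness, disorientation, frustration and confidentiality. The hazard in the first has no counterpart in the second. On VR, the word used for the movements can mean identical to the modified offline forms or identical to the standard 24 forms. Both readings fit, and nothing elsewhere settles it.

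**2. Scheduled hours over 24 weeks** (Procedures Involved; Second-Phase Intervention).
- Responders and switchers: 24 × 1 = 24 h Taichi and 24 h cognitive training, 48 h in all.
- Doubled non-responders: 12 × 1 + 12 × 2 = 36 h Taichi and 36 h cognitive training, 72 h in all; 72/48 = 1.5 times.
- Control: 0 h Taichi and 0 h cognitive training. Education hours are not stated, so total contact is unknown, not zero.
- Phase 1, offline versus VR: 12 h Taichi and 12 h cognitive training in each.

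The contrast exposed to unequal detection is therefore active versus control. The two Taichi modalities are scheduled equally in phase 1.

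**3. How detection enters.** If a proportion d of true events is recorded in each arm, then

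apparent risk ratio = true risk ratio × d(active) / d(control).

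The protocol gives neither d. Purely as an assumed illustration, with d(active) = 0.9 and d(control) from 0.7 down to 0.3, equal true risks would appear as 0.9/0.7 = 1.29 up to 0.9/0.3 = 3.0. This shows the direction and mechanism. It is not an estimate for this trial.

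**4. What counts could show.** Inputs: about 30 per arm (Local Number of Participants) and a response rate of 0.60 (Sample Size and Power Analysis). Equal re-randomisation is assumed.
- Active participants: 30 + 30 = 60. Non-responders: 60 × 0.40 = 24. Doubled: 24/2 = 12, or about 6 per modality.
- One-sided 95% upper bound after zero events in n people: 1 − 0.05^(1/n).

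| n | Group | Upper bound |
|---|---|---|
| 30 | one arm | 9.5% |
| 12 | all doubled | 22% |
| 6 | doubled, one modality | 39% |

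These numbers support description by arm. They do not support testing, or a comparison by dose.

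**The case against.** Several points on the other side stand.

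- A reader might infer that harms cannot be compared at all. That goes too far. Offline and VR Taichi have the same first-phase schedule, and the groups share assessment times at which a common question could be put. The withdrawal section also provides for a final assessment where possible.
- A reader might infer that VR participants perform unmodified movements. The text does not show this. The sentence on VR movements directly follows the modification sentence and may well carry it over.
- A reader might take control contact as nil, or quote an inflation of 1.3 to 3.0. Neither is supported. Education hours are unstated, cognitive training is delivered through a mini-program so not all active hours are shown to be staff contact, and the ratio comes only from assumed detection rates. The monitoring section does not limit monitoring to sessions.
- A reader might treat an excess at doubled dose as detection bias. Doubling raises exposure as well as contact, so the two cannot be separated.
- The protocol has safeguards. It excludes people with exercise contraindications, severe limitation in daily activities or past neurological disease, and it lets investigators withdraw anyone put at risk.
- The analysis of harms, and any harm term in the strategy's objective, may be in an analysis plan that is not shown.

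These points narrow the concern but do not remove it. The risk description and the way events are collected belong in the protocol, and an analysis plan cannot supply control-arm events that were never sought.

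**Conclusion.** The point holds in limited form. The protocol recognises a balance hazard but does not list falls or injury among the risks, and it leaves unclear whether the balance modifications apply to VR Taichi. It assigns responsibility for adverse events without fixing a common enquiry, so active-versus-control counts are open to detection bias of unknown size. That conclusion rests on the stated weekly sessions in the active arms against education and usual care in control, and on the lack of any stated method of asking. Offline versus VR Taichi in phase 1 is not affected in the same way. Even with good collection, precision is poor: an upper bound of 9.5% after zero events in 30, and about 12 people at doubled dose. This is a worthwhile, inexpensive improvement to the harms data. It does not bear on the validity of the cognitive comparisons.

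**What to change.** 1. At the existing week 12 and week 24 assessments, ask all three groups the same short checklist covering the preceding 12 weeks: falls, injury, dizziness or disorientation, soreness or fatigue, and unplanned care.
2. Use the checklist as the main basis for describing harms between arms, and list session-reported events separately.
3. Report the results descriptively by arm beside the recommended strategy. State the 9.5% bound for zero events in 30, and say that counts at doubled dose are too sparse to compare.
4. Reconcile Intervention Components with Risks to Participants, both on falls and injury and on whether the balance modifications apply to VR Taichi. How they are reconciled is for the investigators to decide.

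The cost is a few minutes at two assessments already planned, one table and some protocol wording; no visit is added. The downside is recall: over 12 weeks, people with MCI will under-report minor events, and not necessarily equally in all arms, since weekly sessions may prompt memory and the intervention itself aims to improve cognition. The checklist therefore reduces detection bias without removing it.

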## Provisions to Protect the Privacy Interests of Participants

All research staff will receive training on protecting participant privacy and confidentiality. Interviews and assessments will be conducted in private settings. Data will be de-identified to the extent possible for analysis.

## Consent Process

All potential study participants will be given detailed information about the study in both written and verbal formats. The investigator or designee will explain all aspects of the study in lay language and answer all questions. If the participant decides to participate, they will be asked to sign and date the consent document.

## Setting

The study will be conducted in three randomly selected districts in Shanghai, China. Intervention sessions will take place at community health centers or other suitable venues with appropriate facilities for the Taichi interventions and cognitive training.

